### Pilot study

Based on the experiences of two small pilot innovation programs, the intervention program was developed ([53] and unpublished results [name] and [name] 2009). An Opti-Med pilot study was conducted in two intervention and two control practices for eight weeks including 10 patients. An evaluation was conducted to test the logistics, baseline measurements, questionnaires, and the feasibility and functioning of the expert team of the study. The pilot study resulted in minor changes in the questionnaire instructions, improvements in logistics and communication with the GP practices.

### Process analysis

The process evaluation involves assessing the extent to which the intervention is performed according to the protocol of the study, the time that is spent by the professionals to perform the activities of the protocol, the nature of the recommendations made to the patients by the GP, compliance with these recommendations, the judgment of the GPs, pharmacists and practice nurses about the intervention program. Data on these topics are collected using structured registration forms during the intervention. In addition, semi-structured interviews will be held with the participating practice nurses, GPs and members of the expert teams at the end of the intervention period in order to record their experiences and opinions on the CMR program. The presence and influence of possible contamination in both intervention and control practices will also be assessed by interviewing GPs or practice nurses at the end of the trial on their opinions to what degree structured attention to medication was an issue during the study period in general or with regard to specific patients.

### Sample size

The size of the study groups is based on the difference in change over 6 months between the intervention and control group of the EQ-5D VAS score (score range 0–100). A difference of 7.4 in the EQ-5D VAS is considered as a clinically relevant difference [54]. The average score among persons with osteoarthritis, a comparable group, is 64.8 (standard deviation 26.5). To establish a difference of 7.4 points as statistically significant with alpha = 0.05 and beta = 0.20, a group size of 225 is sufficient, taking the clustered design into account. To adjust for loss to follow up of 10% we will include 500 patients.

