**Methods:**

A cluster randomised controlled trial will be performed in 20 Dutch general practices including 500 patients. Patients of 65 years and older are eligible if they newly present with pre-specified geriatric symptoms in general practice and chronic use of at least one prescribed drug. GP practices will be stratified by practice size and randomly allocated to control (n = 10) or intervention group (n = 10). The intervention consists of CMRs which will be facilitated and prepared by an expert team consisting of a GP and a pharmacist. Primary outcome measures are patient’s quality of life and the presence of self-reported geriatric symptoms during a follow-up period of 6 months. Secondary outcomes are costs of healthcare utilisation, feasibility, number of drug related problems, medication adherence and satisfaction with medication.

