### Primary outcome measures

Quality of life (QoL) will be assessed using both the SF-12 and the EuroQol (EQ-5D-3 L) at baseline, and after 3 and 6 months. The SF-12 covers eight dimensions of health with two summary scores; physical health (PHS) and mental health (MHS), and has been validated in many different countries and populations [39–42]. The PHS will be used as outcome measure because of its superior responsiveness compared to the MHS [43]. The EQ-5D-3 L is a generic preference based health status measure that has been shown to be valid and reliable in a variety of populations and patient groups [44, 45]. The EQ-5D-3 L will be assessed using information from the patient and by proxy assessment by an informal carer and a healthcare professional. The proxies will be asked to report on QoL from the patients’ perspective [46]. The EQ-5D scores will be used to calculate utilities using the Dutch tariffs. Quality-adjusted life years (QALYs) will be calculated using linear interpolation between time points. Higher QALY scores indicate more improvement in quality of life [47].

The presence of geriatric giants will be assessed at baseline with the screening questionnaire. At 3 and 6 months, presence of geriatric giants will be assessed with the same questions as in the screening questionnaire enabling to assess changes compared to baseline.

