Quality of life is the primary outcome measure. This may not be sensitive enough to capture the changes induced by the intervention. However, we have chosen to use generic health measures as primary outcome measures because we include patients in this study that might have a variety of geriatric symptoms with a heterogeneous treatment effect. Also we think that in this population quality of life is the most important outcome.

In addition, the study is not blinded and there is a possibility of contamination between the intervention and control group. We counter possible contamination between treatments groups by using a cluster randomised controlled design. That way, caregivers cannot unintentionally apply aspects of the Opti-Med study into their usual care for patients. Patients in the control condition also fill out the screening questionnaire on actual drug use and medication related problems, this is needed for the study, but could underestimate the effectiveness of Opti-Med by increasing awareness of possible drug related problems in these control participants. Furthermore, we suppose that current activities on older people care and possible future pharmacist’s polypharmacy projects are minimally interfering with the study. This assumption about possible contamination will be checked during the process analysis.

Implementation of structured CMR and monitoring will raise the awareness about the importance of optimising medication use in general, and especially in older patients among healthcare professionals. In this study, we will evaluate a form of a structured CMR that can easily be implemented in a GP cooperation or care group. If the CMR is shown (cost-) effective and feasible it could also be extrapolated to other groups of patients in the future in whom inappropriate medication use is suspected as well. If proven cost-effective, this will support the nationwide implementation of this structured approach. The first results of the study will be expected at the end of 2015.

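### The sample size rests on the EQ-5D VAS, a score not named among the primary outcomes, and the article does not settle which primary outcome leads

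*Protocol article*

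**What the plan says.** Protocol article, Sample size: the group size is derived from the "difference in change over 6 months between the intervention and control group of the EQ-5D VAS score", on a 0–100 range. "A difference of 7.4 in the EQ-5D VAS is considered as a clinically relevant difference", and the SD of 26.5 comes from a reference group with osteoarthritis. The difference is to be detected as "statistically significant with alpha = 0.05 and beta = 0.20", giving 225 per group after an allowance for clustering and 500 patients after 10% loss.

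Primary outcome measures: quality of life is measured by the SF-12 and the EQ-5D-3L at baseline, 3 and 6 months. For the SF-12, "The PHS will be used as outcome measure because of its superior responsiveness compared to the MHS". For the EQ-5D, "The EQ-5D scores will be used to calculate utilities using the Dutch tariffs", and QALYs follow from these. The presence of geriatric giants, at 3 and 6 months, is listed in the same section. The EQ-5D VAS is named neither here nor under Secondary outcome measures.

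Abstract, Methods: the primary outcomes are quality of life and "the presence of self-reported geriatric symptoms during a follow-up period of 6 months". Discussion: "Quality of life is the primary outcome measure".

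Statistical analyses: the groups are compared on the outcome measures by multilevel linear and logistic models, with no outcome or time point put first.

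**The concern.** A power statement is useful only if it refers to the outcome on which the trial will be judged. Here it refers to a 0–100 self-rating, while the outcome section names a tariff-based utility with its QALYs, an SF-12 summary score and the presence of symptoms. These are on other scales and are not interchangeable with the VAS.

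The second difficulty is that the article does not settle what is primary. Two domains appear in the Abstract and in the outcome section, one of them measured by two instruments; one sentence in the Discussion names a single domain. If the physical score improved and the utility did not, or symptoms improved and neither quality-of-life score did, the article gives no agreed reading. Patients and practices are unblinded and these outcomes are mainly self-reported, so the lead result should not be open to choice after the data are seen.

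**Working it through.** **1. The plan's own figure.** Inputs from Sample size: difference 7.4, SD 26.5, alpha 0.05 (taken as two-sided, since sidedness is not stated), power 0.80.

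n per group before clustering = 2 × [SD × (z₀.₉₇₅ + z₀.₈₀) / difference]² = 2 × [26.5 × (1.960 + 0.842) / 7.4]² = 201.3, so 202.

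The stated 225 implies a design effect of 225 / 201.3 = 1.118. No intracluster correlation is given, so 225 cannot be reproduced from stated inputs alone. With 22.5 patients per practice (225 over 10 practices), 1.118 corresponds to a correlation of (1.118 − 1) / 21.5 ≈ 0.0055. The loss step reproduces: 450 / 0.90 = 500. All of this concerns the EQ-5D VAS only.

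**2. Sized score against named scores.**

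| Score | Named as primary | Effect size, SD or rate given |
|---|---|---|
| EQ-5D VAS, 0–100 | No | 7.4; SD 26.5 |
| EQ-5D utility / QALY | Yes | None |
| SF-12 physical score | Yes | None |
| Presence of geriatric giants | Yes | None |

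The other VAS scales in the article (Screening questionnaire, Inclusion procedure, Economic evaluation) are 0–10 symptom or pain scales, not the EQ-5D VAS. The standardised difference, 7.4 / 26.5 = 0.28, is specific to the VAS. Power for the three named scores cannot be computed from the article.

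**3. What is primary.** Abstract: two domains. Primary outcome measures: the same two, with two instruments for quality of life, at 3 and 6 months. Discussion: one domain. Study design points to 6 months for assessing effects, but neither Primary outcome measures nor Statistical analyses ranks 6 months above 3.

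**4. Conditional illustration of multiplicity.** Suppose each primary were tested at two-sided 0.05 and any one success counted. Under independence the familywise error is 1 − 0.95^k:

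- k = 2 (the two domains): 1 − 0.95² = 9.75%
- k = 3 (physical score, EQ-5D, geriatric giants): 1 − 0.95³ = 14.3%

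With equicorrelated normal test statistics at an assumed correlation of 0.5, simulation gives 9.1% and 12.5%.

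If alpha were split equally instead, at the VAS standardised difference and the implied design effect (effective n = 225 / 1.118 = 201.3), power = Φ(2.802 − z₁₋α/₂):

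- two primaries, alpha 0.025: Φ(2.802 − 2.241) = 71%
- three primaries, alpha 0.0167: Φ(2.802 − 2.394) = 66%

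**The case against.** The EQ-5D-3L is a listed primary instrument, and the VAS may have been meant as part of it. The utility sentence can be read as preparing the QALY calculation rather than as excluding other scores. This stands in part: it is too strong to say that the trial was sized on something foreign to its primary outcomes. But the section does state which scores it takes from each instrument, and the VAS is not among them.

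The sentence in the Discussion may be loose wording, since the same paragraph goes on to speak of primary outcome measures in the plural. That is possible, but both uses there concern generic health measures, and geriatric symptoms are not included.

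A reader might infer that several primaries share one unadjusted 0.05 and that any one of them could be declared a success. The article does not say so. Its only alpha is a sample-size input, and a testing rule could lie in an analysis plan that is not shown. If success required every primary, the error would not inflate; power would fall instead.

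A reader might also count eight tests (physical score, EQ-5D, five symptom scales, falls) and quote 1 − 0.95⁸ = 34%. That assumes each symptom is tested separately and independently, which is not stated; one composite fits the text equally well. Nor do the 3-month and proxy data clearly add tests: repeated measurements enter a multilevel model, and the Outcome measures section describes proxy ratings as a possible substitute for self-report.

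**Conclusion.** The point holds as a mismatch and an inconsistency within the article. The 80% power belongs to the 6-month change in the EQ-5D VAS, which is not named as primary; for the scores that are named, power is undetermined. The sections also disagree on whether geriatric giants are primary, and no lead score or time point is fixed. None of this depends on an unseen analysis plan, because choosing the primary outcome and matching the sample size to it are protocol decisions.

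Inflation of the error rate is not established. The figures of about 9–10% for two primaries and 12–14% for three hold only if each is tested at 0.05 and any single success counts, over correlations from 0.5 down to independence.

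**What to change.** In Primary outcome measures, name one lead score and time point that matches Sample size: the patient-reported change in EQ-5D VAS at 6 months. If another score is to lead, restate the power in Sample size for that score at the planned 500 patients, with its own difference and SD or rate.

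Make the Abstract, Primary outcome measures and Discussion agree on that lead outcome and on the standing of geriatric giants. Test the remaining primary outcomes in a fixed order or by Holm within 0.05, and label the 3-month and proxy results as supportive.

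If the EQ-5D VAS leads, this is wording only, provided the VAS is being recorded, as the sample-size basis implies; no patients or visits are added. The downside is a stricter threshold for the outcomes that do not lead. The change should be made before outcome data are seen.

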### Study design

A cluster randomised clinical trial will be performed in 20 general practices including 500 patients (see Figure 1). Allocation of the intervention and control condition will be carried out randomly at practice level. Eligible patients will be invited to participate in the study and the medication of the patients listed in the intervention practices will be reviewed. Patients listed in the control practices will receive usual care, with no systematic attention for their medication. The effects of this intervention will be assessed after a follow-up period of 6 months. The rationale to use a cluster design at practice level is to prevent contamination of structural attention to CMR activities within the GP practice.

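### The 225 per group allows for clustering by a factor of only 1.118, so the stated 80% power holds for an unadjusted comparison only at an ICC of about 0.005 or less

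*Protocol article*

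**What the plan says.** The Sample size section of the protocol article bases the size on "the difference in change over 6 months between the intervention and control group of the EQ-5D VAS score (score range 0–100", on the 0–100 scale. The target is given as "A difference of 7.4 in the EQ-5D VAS is considered as a clinically relevant difference". The variability comes from another population: "The average score among persons with osteoarthritis, a comparable group, is 64.8 (standard deviation 26.5". The error rates are those for a result that is "statistically significant with alpha = 0.05 and beta = 0.20". On these inputs it concludes that "a group size of 225 is sufficient, taking the clustered design into account", and then: "To adjust for loss to follow up of 10% we will include 500 patients".

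The cluster structure is given in the Study design section: "A cluster randomised clinical trial will be performed in 20 general practices including 500 patients". The Abstract adds that 10 practices go to each arm. The Statistical analyses section plans multilevel models for clustering and for repeated measurements within a patient. It gives examples of covariates (sex, age, education, number of drugs, multimorbidity), and the baseline score is not among them.

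**The concern.** The article prints every input of a two-group comparison of means, and also the result. The allowance for clustering is therefore not hidden: it is the ratio of 225 to the unclustered size, and that ratio is small for practices that supply over 20 patients each. A reader who sees that clustering was taken into account will take 80% power as a property of the design. On the printed inputs it is a property only if practices hardly differ.

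The SD raises a second question. The paragraph speaks of change over 6 months, but 26.5 describes a score at one time point.

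What is at stake is how a null result is read. The Discussion itself concedes that quality of life may be too insensitive to register the intervention's effect. If true power for 7.4 points is nearer 65% than 80%, failing to find the difference says less about it than the stated power suggests.

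**Working it through.** **Inputs from the article.** Difference 7.4; SD 26.5; alpha 0.05 (sidedness not stated, two-sided taken); power 80%; 225 analysed per group; 10 practices per arm; 10% loss; 500 recruited. Patients per practice: 225/10 = 22.5 analysed, 500/20 = 25 recruited.

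**1. The article's own figures.**
- Loss to follow-up: 450/0.9 = 500. This reproduces. It is a separate step and adds no room for clustering.
- Unclustered size: n = 2 × (1.96 + 0.8416)² × 26.5² / 7.4² = 201.3 per group.
- With an assumed ICC of 0.005 and 25 patients per practice, the design effect is 1 + 24 × 0.005 = 1.12, and 201.3 × 1.12 = 225.5. So 225 can be reached with a round ICC, though the article states none.

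**2. Implied allowance.**
- Design effect = 225/201.3 = 1.118.
- ICC = (design effect − 1)/(m − 1) = 0.118/21.5 = 0.0055 with m = 22.5, or 0.118/24 = 0.0049 with m = 25.

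**3. Power with 225 per group.** SE = 26.5 × √(2 × DE/225), with DE = 1 + 21.5 × ICC. At ICC 0, SE = 2.498 and 7.4/SE = 2.96. Normal power is Φ(7.4/SE − 1.96). The other column uses a non-central t with 20 − 2 = 18 df. The ICC values are assumptions.

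| ICC | DE | Power, normal | Power, 18 df |
|---|---|---|---|
| 0 | 1.000 | 84.2% | 80.0% |
| 0.0055 | 1.118 | 80.0% | 75.5% |
| 0.01 | 1.215 | 76.6% | 72.0% |
| 0.02 | 1.430 | 69.7% | 64.9% |
| 0.05 | 2.075 | 53.8% | 49.4% |

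Using 18 df consumes the whole allowance: 80.0% is reached at ICC 0 and at no positive value. The difference detectable with 80% power on 18 df is 7.4, 8.2, 8.9 and 10.7 at ICC 0, 0.01, 0.02 and 0.05.

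**4. SD of change.** With equal SDs at both times and correlation r between baseline and 6 months, SD of change = 26.5 × √(2(1 − r)).
- r = 0.4: 29.0
- r = 0.5: 26.5
- r = 0.6: 23.7

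The figure used is thus right for change only at r = 0.5. At r = 0.4 a plain change score has 77% power with no clustering at all (normal test). At r = 0.6 the size needed falls to 201.3 × 0.8 = 161, leaving room for an ICC of 0.0185.

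**5. Adjustment for baseline.** The variance is multiplied by (1 − r²), with the same ICC assumed to apply after adjustment. At ICC 0.02 and 18 df, power with 225 per group is 77% at r = 0.5 and 83% at r = 0.6, against 65% unadjusted.

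**The case against.** The strongest case on the other side has four parts.

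- **No calculation is wrong.** A round ICC of 0.005 with 25 patients per practice gives 225.5, so clustering may well have been allowed for as stated, and an article may leave the ICC to the full protocol. This stands: a reader might infer an arithmetic slip or a forgotten design effect, and the text supports neither. The absence of an ICC is not the point. The printed inputs and result together fix the allowance at 1.118, and no unseen document can alter that ratio while they stand.
- **Nothing in the article shows that 0.005 is too low.** The range 0.01 to 0.05 is assumed. Stable differences between practices also cancel in a change, so the relevant ICC is that of the quantity analysed. This stands too. It makes the power conditional; it does not justify a flat figure.
- **The analysis may do better than the calculation.** The planned models use repeated measurements. With baseline adjustment at r = 0.5 and a normal test, 225 per group tolerates an ICC of 0.023. The Sample size section, however, claims no such gain and states no correlation. The 18 df is likewise a choice of this check; the article names no method. The normal-test column does not depend on it, and still falls below 80% above an ICC of 0.0055.
- **The harm is limited.** The calculation concerns the EQ-5D VAS, which the Primary outcome measures section does not name, and a null result should be read from its confidence interval in any case. This tempers the consequence but does not correct the statement.

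A one-sided test at 0.05 would need 159 per group and leave room for an ICC of 0.019, but none is stated.

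**Conclusion.** The point holds as a misstated, conditional power claim. For an unadjusted comparison on the article's inputs, 80% power for 7.4 points requires an ICC of at most about 0.005 with a normal test, and of 0 with a test on 18 df. Over assumed ICCs of 0.01 to 0.05, power runs from 77% to 54% (normal) or from 72% to 49% (18 df). The cross-sectional SD applied to a change outcome adds an error whose direction the article does not reveal.

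It is tempting to go further and call the trial underpowered. The article does not support that: it gives neither the ICC nor the correlation between baseline and follow-up, and adjusting for baseline could bring power back to 80% or above under some of the assumed values. These conclusions rest on a two-sided test, equal practice sizes and 22.5 analysed patients per practice. This should be fixed, but it is not a must-fix.

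**What to change.** **Sample size section.** Replace the flat 80% with the unclustered size (201), the assumed ICC, the cluster size, the resulting design effect and the SD of the quantity actually analysed, whether score, change or baseline-adjusted score. If the last two are meant, state the correlation assumed. Then give the power for 7.4 points with 225 per group over a plausible range of ICC, using degrees of freedom suited to 20 practices.

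**Statistical analyses section.** Name the baseline value of the outcome as a covariate in the models for continuous outcomes. The SF-12, the EQ-5D and the symptom scales are already recorded at baseline, so nothing new is collected. On the assumptions above, this lifts power at ICC 0.02 with 18 df from 65% to about 77% (correlation 0.5) or 83% (correlation 0.6).

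**Cost.** Rewording of one paragraph and one added covariate. No extra patients or practices are asked for. The downside is a stated power that looks less favourable.

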### Statistical analyses

Descriptive statistics will be used to describe the study population. Dropout and loss to follow up will be described. Effect analyses will be performed according to both ‘intention to treat’ and per protocol principles. Differences between intervention and usual care patients on the outcome measures will be compared between the intervention and control group by both univariate and multivariate techniques. Multilevel linear and logistic regression analyses will be performed to study differences between the intervention and the control patients. Multilevel analysis is needed in order to take clustering on the GP level and repeated measurements in one patient into account. We will adjust for possible confounders, such as gender, age, education level, number of medications and multi-morbidity.

Possible future subgroup analyses will be exploratory, due to lack of power.

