### Randomisation

Randomisation will be performed by a statistician blinded to characteristics of the practices using a computer generated list of random numbers. The practices are stratified by practice size (two strata), to ensure equally sized groups. Before patients are recruited, participating practices will be randomly allocated to the intervention, or control condition. Patients will be allocated to either one of the treatment conditions, based on the practice where they are listed. Blinding of patients, GPs and practice nurses to treatment allocation is not possible due to the nature of the intervention.

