### Economic evaluation

For the economic evaluation, missing cost and effect data will be imputed using multiple imputation according to the Multivariate Imputation by Chained Equations (MICE) algorithm developed by van Buuren using predictive mean matching and fully conditional specification [55]. The number of imputed datasets will be increased until the fraction of missing information is below 5% [56]. The imputed datasets will be analysed separately as described below and subsequently pooled using Rubin’s rules.

The effect measures that will be taken into account in the cost-effectiveness are QALYs, and changes in the VAS scores of the geriatric giant symptoms. For effects and costs, linear multilevel regression models will be estimated. Clustering at the level of GP practice will be included in these multilevel models. Incremental cost-effectiveness ratios (ICERs) will be calculated by dividing the difference in mean total costs between the treatment and control groups by the difference in mean effects between the groups. Costs generally have a highly skewed distribution; therefore, bootstrapping with 5,000 replications will be used to estimate bias-corrected and accelerated confidence intervals around cost differences [57]. To account for the clustering of data, bootstrap replications will be stratified for practice [58]. The uncertainty surrounding the ICERs which will be graphically presented on cost-effectiveness planes. Cost-effectiveness acceptability curves and net monetary benefits will also be calculated. Cost-effectiveness acceptability curves show the probability that the medication review programme is cost-effective in comparison with usual care for a range of different ceiling ratios thereby showing decision uncertainty.

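### The effect model puts clustering at GP level although practices were randomised, and names neither baseline outcome nor practice-size stratum; the QALY total is called improvement although it contains baseline utility

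*Protocol article*

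**What the plan says.** All references are to the protocol article.

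- **Unit of allocation.** Study design: "Allocation of the intervention and control condition will be carried out randomly at practice level". The abstract gives 10 practices per arm.
- **Stratification.** Randomisation: "The practices are stratified by practice size (two strata), to ensure equally sized groups".
- **Clustering in the effect analysis.** Statistical analyses: "Multilevel analysis is needed in order to take clustering on the GP level and repeated measurements in one patient into account".
- **Clustering in the cost-effectiveness analysis.** Economic evaluation: "Clustering at the level of GP practice will be included in these multilevel models". The bootstrap there is also stratified by practice.
- **Adjustment variables.** Statistical analyses: "We will adjust for possible confounders, such as gender, age, education level, number of medications and multi-morbidity". The baseline value of the outcome and practice size are not in the list, although the list is open.
- **Baseline data.** The section on primary outcomes states: "Quality of life (QoL) will be assessed using both the SF-12 and the EuroQol (EQ-5D-3 L) at baseline, and after 3 and 6 months". Geriatric symptoms are also recorded at baseline, through the screening questionnaire. Sample size sets its target as a between-group difference in six-month change.
- **QALYs.** They are computed by linear interpolation between time points and then described so: "Higher QALY scores indicate more improvement in quality of life". Economic evaluation names practice clustering for the effect regression but no adjustment for baseline utility.

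**The concern.** The article gives two cluster levels for one trial, and the one attached to the primary effect analysis is not the unit that was randomised. If several GPs share a practice and the model has a random effect for GP only, patients of different GPs in the same practice are treated as independent. The treatment contrast is between practices, so its standard error would be too small.

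The other parts do a different kind of harm. Leaving the baseline outcome out costs precision. Leaving the stratum out costs precision or makes the standard error conservative. Neither makes it too small.

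The QALY sentence matters because only 20 practices are randomised and patients are recruited, unblinded, after allocation. A baseline difference in utility between arms is therefore a realistic possibility. A QALY total carries that difference into the effect estimate unless the model removes it.

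**Working it through.** **1. The plan's own sample size.** Inputs from Sample size: difference 7.4, SD 26.5, alpha 0.05 (two-sided assumed), power 0.80, 225 per group, 10% loss.

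- Without clustering: 2 × [26.5 × (1.960 + 0.842) / 7.4]² = 201.3, so 202 per group.
- 225 / 201.3 gives a design effect of 1.118. With 22.5 evaluable patients per practice (225 / 10), the implied ICC is 0.118 / 21.5 = 0.0055. The article states no ICC.
- 225 / 0.9 = 250 per group, so 500 in total reproduces exactly.

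**2. A literal GP-level random effect.** Assume G GPs per practice and all correlation at practice level, with m = 22.5.

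- True variance of a practice mean (in units of total variance): ICC + (1 − ICC)/m.
- Variance under the GP-only model: ICC/G + (1 − ICC)/m.
- SE ratio = square root of (GP-only / true). Type I error = P(|Z| > 1.96 × ratio).

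Example, G = 3 and ICC 0.02: true 0.0636, GP-only 0.0502, ratio 0.889, type I error 8.1%.

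| ICC | G = 1 | G = 2 | G = 3 | G = 5 |
|---|---|---|---|---|
| 0.0055 | 5.0% | 5.7% | 5.9% | 6.1% |
| 0.02 | 5.0% | 7.2% | 8.1% | 9.0% |
| 0.05 | 5.0% | 9.4% | 11.7% | 14.0% |

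The number of GPs per practice is not in the article, and the ICCs of 0.02 and 0.05 are assumptions.

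**3. Baseline adjustment against a change score.** With correlation r between baseline and follow-up, the variance factor relative to a follow-up-only comparison is 1 − r² for baseline adjustment and 2(1 − r) for a change score. The same r is taken to apply within and between practices. With ICC 0.02 (assumed) the design effect is 1 + 21.5 × 0.02 = 1.43, and SE = 26.5 × √factor × √(2 × 1.43 / 225) = 2.988 × √factor. Power for 7.4 comes from the non-central t distribution with 20 − 2 = 18 df.

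| r | Change-score factor | Power | Baseline-adjusted factor | Power | Gain |
|---|---|---|---|---|---|
| 0.5 | 1.00 | 65% | 0.75 | 77% | 12 points |
| 0.6 | 0.80 | 75% | 0.64 | 83% | 9 points |
| 0.7 | 0.60 | 86% | 0.51 | 91% | 5 points |

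Gains are taken from unrounded powers. The effect of naming the practice-size stratum cannot be quantified from the article.

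**4. The QALY total.** With utilities u0, u3 and u6 at 0, 3 and 6 months, linear interpolation over half a year gives 0.125·u0 + 0.25·u3 + 0.125·u6. This is a level that includes the baseline, not a change. A patient with high but falling utility can score above one who improves from a low start.

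Suppose the arms differ by 0.03 in baseline utility, treatment has no effect, and the regression of each follow-up utility on baseline has slope 0.6 (correlation 0.6 with equal SDs, assumed). The QALY difference is then 0.03 × (0.125 + 0.375 × 0.6) = 0.03 × 0.35 = 0.0105. An imbalance of 0.03 is about one standard error: 0.25 × √[2 × (1 + 24 × 0.02) / 250] = 0.027, with an assumed utility SD of 0.25 and ICC of 0.02.

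**The case against.** GP level may be shorthand for the general practice. Study design randomises practices and gives contamination within the practice as the reason for clustering, and Economic evaluation models the practice. On that reading there is no inflation. This stands: a wrong model is not established, only a conflict in wording that should be resolved.

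A reader might infer that the effect model omits baseline. The article does not support that. The covariate list is illustrative, the model covers repeated measurements that may include baseline as a response, and both Sample size and Primary outcome measures speak of change from baseline. All that can be said is that the baseline outcome and the stratum are not named and that the way baseline enters is not stated. For the same reason, the larger gains obtained against a follow-up-only analysis (from 65% to 77%, 83% or 91%) use a comparator that the article never proposes. The change-score comparison is the fair one.

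It can also be said that a condensed article leaves the full covariate list to the full protocol or analysis plan. This weakens the covariate part considerably. It does not remove the conflict between the two cluster levels or the misdescription of the QALY total, both of which are stated in the text.

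Finally, Economic evaluation lists no covariates at all, so its silence on baseline utility is not a decision to exclude it. That is fair. However, the article's own description of QALYs as a measure of improvement suggests that the need for adjustment could be missed.

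**Conclusion.** The point holds in a limited form.

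- **Firmest part:** the effect analysis names GP level while randomisation and the economic analysis use the practice. The consequence ranges from nothing (one GP per practice, or GP level meaning practice), through about 6% type I error at the ICC implied by the plan's sample size, to 7% to 14% at ICCs of 0.02 to 0.05 with 2 to 5 GPs per practice. The upper range needs the literal reading, all correlation at practice level, and ICCs that the article does not give.
- **Precision:** naming the baseline outcome as a covariate is worth about 12, 9 or 5 power points over a change score at r = 0.5, 0.6 or 0.7, with ICC 0.02 assumed. Naming the stratum matches the analysis to the design, without a gain that can be put in figures here.
- **QALYs:** the descriptive sentence is wrong as it stands. An unadjusted regression would turn a 0.03 baseline imbalance into a QALY difference of about 0.01 under the stated assumptions.

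A reader might conclude that all three gaps make standard errors too small. Only the cluster level could do so.

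**What to change.** 1. In Statistical analyses, replace GP level with practice level. A random effect for GP within practice may be added but should not replace the one for practice.
2. In the same section, name the baseline value of each outcome and the practice-size stratum as fixed covariates, alongside the patient characteristics already listed.
3. In Economic evaluation, add baseline utility as a covariate in the QALY regression.
4. In Primary outcome measures, reword the QALY sentence to say that a higher total reflects better quality of life over the six months, baseline included.

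The cost is one or two extra parameters per model and a few changed sentences. No new data are needed, since the baseline outcomes and practice size are already collected.
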